### Randomization

Randomization lists per center will be prepared at UMC Utrecht, using *nQuery Advisor* in permuted blocks of 4; randomization lists are safeguarded at the UMC Utrecht. Randomization data will be incorporated in the decision-making software application that is used in each of the institutes. This way, on-site research staff, patients, and sponsor trial personnel will remain blinded to treatment strategy. A patient will be allocated to the HandScan or DAS arm, as soon as baseline clinical data are entered into the software application. A patient-specific study number and the year of birth will function as identifiers. Unblinding will not be necessary as both arms receive identical medication in an open fashion.

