### Assessments

Patients will visit the outpatient clinics monthly (Fig. 1). At each visit, disease activity will be measured, to ensure blinding both with HandScan and DAS44, consisting of serum CRP, a 44 joints assessment for swelling and tenderness, and a PGA (VAS 0–10 cm, 10 = worst). At baseline and 3, 6, 12, and 18 months patients will fill out the HAQ (first outcome), the Short Form Health Survey (SF36), EuroQol (EQ5D), and the questionnaire on direct and indirect costs (second outcome). Direct costs (health care) and indirect costs (loss of paid and household productivity) will be calculated from questionnaires, including the Health and Labour questionnaire [13]. Radiographs in the antero-posterior direction of hands, wrists, and feet will be obtained at baseline and 18 months (second outcome). The current gold standard for scoring these radiographs is the Sharp/van der Heijde scoring method [11]. This method scores erosions (score 0–5 per region) and joint space narrowing (score 0–4 per region) of these joints and sums the scores to the SHS score, ranging from 0 to 448. A newly developed fully automated radiographic scoring system of hand and wrist joints is also applied to quantify changes in the joint space width over time.

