### Definitions of remission

Aimed at predefined remission criteria, treatment is intensified in a similar fashion for both arms, according to a predefined schedule. In the DAS arm, remission is defined based on the ACR/EULAR 2011 Boolean remission criteria, all of which must be met [14]:TJC ≤ 1 of 44 joints: sternoclavicular, acromioclavicular, shoulder, elbow, wrist, metacarpophalangeal (MCP), proximal interphalangeal (PIP), metatarsophalangeal (MTP), knee, and ankle jointsSJC of 30 small joints (MCP, PIP, and MTP joints) ≤ 1 AND SJC of 14 large and other joints (sternoclavicular, acromioclavicular, shoulder, elbow, wrist, knee, and ankle joints) = 0CRP ≤ 1 mg/dlPGA ≤ 1 (on VAS 0–10 cm, 10 = worst)

In the HandScan arm, remission is defined based on the following HandScan criteria, all of which must be met:Total optical joint score per patient ≤ 11(based on ROC curves in a comparative study with DAS28 and ultrasonography) [6, 7]≤ 1 joint per patient with an optical score of > 1

The optical joint scores are shown by the HandScan shortly after assessment (see screen shot of the HandScan in Fig. 2).

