### Implementation of a software application for patient-tailored, tight-control treatment

Although treatment regimens and dosing steps are identical for all patients, actual medication will differ considerably between patients in this study, as the study protocol tailors treatment to every patient in a treat-to-target strategy (Fig. 3). To account for these variations in treatments and to allow for double-blind treatment, a decision-making software application was developed. It uses a data trail (data log) of current and previous patient-specific input to check, e.g., for consistent discordance between remission criteria and prevent drug dosages higher than previous MTD in case of a flare. At each visit, the patient identification number, year of birth, and parameters for both clinically and HandScan-assessed disease activity will be entered into the application. Based on whether there is remission or not, according to the criteria of the randomized arm, the application will provide the next patient-specific medication step.

The application was developed and tested to conform to the regulations and guidelines for the development of a medical appliance class I and medical software class B (*EN 62304 Medical device software –Software life-cycle processes, EN 62366 Usability, ISO 14971 Medical devices – Application of risk management to medical devices*).

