## Discussion

This study aims to evaluate clinical efficacy of a HandScan-guided versus DAS-guided tight-control and treat-to-target treatment strategy for early RA. The HandScan guidance has potential drawbacks, mainly because it relies solely on arthritic activity in hands and wrists. However, optical spectral transmission (OST) did correlate to DAS28 in a previous study [6], as well as to US assessed synovial inflammation of hand and wrist joints, while DAS28 did not correlate with these US results. It is possible that, considering the strengths and weaknesses of both guidance methods, the optimal guidance for future treatment of early RA would be using both methods or a combination of parameters of both methods (e.g., HandScan with CRP measurement).

An economic evaluation of guidance of a tight-control strategy using the HandScan has been previously published [17]. Implementation of the HandScan as a monitoring tool was modeled at comparable costs and comparable effects as using clinical assessments. To validate this result, cost-effectiveness in the current study will be calculated based on actual data (i.e., a trial-based economic evaluation); this approach requires less assumptions and therefore has a lower risk of bias.

This protocol describes a specifically designed software application to allow for double-blind, safe, and patient-tailored guidance of treatment. Implementation of the software application has the advantage that it allows for on-site patient randomization and double-blind (for the guidance method) treatment. Deviation from standard treatment schedules is allowed, for example, by defining a MTD or the opportunity to switch from MTX to LEF in case of MTX intolerance. Three consecutive discrepancies in medication advice between the HandScan and DAS arm lead to switch of the respective patients in the HandScan arm to the DAS arm as a built-in safety for potentially large differences between arms. Importantly, as neither the patient nor the physician is aware of a switch, the double-blind design will be maintained.

This specifically designed decision-making software application also allows for implementation of other RCTs testing future, novel methods of guidance of tight-control and treat-to-target treatment strategies in RA.

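### The software conceals the randomization list, but staff can often infer the guiding method when the two criteria call for different medication steps, so the unqualified double-blind claim is not supported

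*Protocol article*

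**What the plan says.** The Abstract and the opening of Methods/design call the trial double-blind. The Randomization section says the allocation data sit inside the decision software and concludes: "This way, on-site research staff, patients, and sponsor trial personnel will remain blinded to treatment strategy". The same section says that both arms receive their medication openly. The Discussion extends the claim to the covert move of discordant HandScan-arm patients to DAS guidance: "as neither the patient nor the physician is aware of a switch, the double-blind design will be maintained".

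The blinding device is double measurement. Under Assessments, disease activity is measured monthly in every patient, "to ensure blinding both with HandScan and DAS44".

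Other sections describe what can be seen at the site:

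- Definitions of remission gives both rules in full. For the DAS arm, "remission is defined based on the ACR/EULAR 2011 Boolean remission criteria, all of which must be met". For the HandScan arm, the total score must be at most 11, with "≤ 1 joint per patient with an optical score of > 1".
- The same section says of the HandScan result: "The optical joint scores are shown by the HandScan shortly after assessment".
- The section on the software application says that at each visit "parameters for both clinically and HandScan-assessed disease activity will be entered into the application". Depending on whether there is remission "according to the criteria of the randomized arm, the application will provide the next patient-specific medication step".
- Under Treatment strategy, non-remission leads to the next escalation step. Remission leads to unchanged treatment, and to tapering once it has lasted three months.

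**The concern.** Concealing a list blinds people only if they cannot work out its content from what they see. Here the output of the software depends on the arm, and its inputs and rules are known at the site. The advice can therefore disclose which rule produced it.

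This matters because several quantities in the trial depend on judgment. The primary outcome, the HAQ, is patient-reported. Guidance by the clinical criteria depends on joint counts and on the PGA. The Patient safety section also foresees departures from protocol on clinical judgment. Knowledge of the guiding method could influence any of these. The documents do not allow the direction or size of such an effect to be worked out. The harm that can be stated with certainty is that the report would claim a property that the described procedures do not secure.

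**Working it through.** There is no stated figure to reproduce, so the check is mainly logical.

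**Step 1: what the advice discloses.** At an ordinary escalation step, before any switch:

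| Clinical criteria | HandScan criteria | Step if DAS guides | Step if HandScan guides |
|---|---|---|---|
| remission | remission | unchanged or taper | unchanged or taper |
| not remission | not remission | intensify | intensify |
| remission | not remission | unchanged or taper | intensify |
| not remission | remission | intensify | unchanged or taper |

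In the last two rows the step fits only one rule. Anyone who holds both results and the advice can name the guiding method.

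**Step 2: the HandScan score is not needed.** The clinical rule requires every component to be met, so one failed component (a PGA above 1, for instance) settles clinical non-remission. If the advice is then unchanged treatment at an ordinary escalation step, the clinical rule did not produce it. The same holds if all clinical components are met and the advice is to intensify. This route works in one direction: a mismatch points to HandScan guidance, while the absence of mismatches only suggests DAS guidance.

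**Step 3: where the inference fails.**

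- Both rules can give the same step. The last three rows of Table 2 (anti-TNF) are identical, and its footnote fixes hydroxychloroquine at three months in every scenario.
- The step may be driven by adverse events or by a previously established maximum tolerable dose.
- After a covert switch, a HandScan-arm patient's advice follows DAS. A later discordant visit, taken alone, points to the wrong arm.

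**Step 4: illustration of frequency.** The documents give no discordance rate. Let p be the *assumed* probability that a visit is decision-discordant, with visits independent. Then P(at least one in m visits) = 1 − (1 − p)^m. Monthly visits give about m = 17 decision visits after baseline and before month 18; m = 6 covers the first six.

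- p = 5%, m = 6: 1 − 0.95^6 = 1 − 0.735 = 0.265.
- p = 30%, m = 6: 1 − 0.70^6 = 1 − 0.118 = 0.882.

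The last column gives, under the same assumption, the chance of three consecutive discordant visits within 17. It comes from a visit-by-visit recursion on the current run length (0, 1 or 2), absorbing at 3.

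| Assumed p | At least one in 6 | At least one in 17 | Three in a row within 17 |
|---|---|---|---|
| 5% | 26.5% | 58.2% | 0.2% |
| 10% | 46.9% | 83.3% | 1.4% |
| 20% | 73.8% | 97.7% | 9.5% |
| 30% | 88.2% | 99.8% | 26.7% |

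If discordance clusters within patients, as is likely, the *at least one* columns fall and the last column rises for the same p.

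**The case against.** The strongest objection is that no sentence says one person sees the HandScan score, the clinical findings and the advice. The Background says an assistant without medical training can run the device, and the text does not say to whom the score is shown or who enters the data. The full protocol may separate these roles, and an article may leave that out. This stands as a limit: that the same staff see everything is an inference. It does not rescue the claim, because Step 2 needs only the clinical findings and the open advice.

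Four stronger readings are tempting, and the documents do not support them:

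- *Every discordant visit reveals the arm.* It does not; Step 3 lists the exceptions.
- *Patients are unblinded.* A patient knows their own PGA and prescription, but nothing says that patients see the optical score, know the thresholds or learn their clinical classification. Access by sponsor personnel is likewise not shown.
- *The share of patients affected can be derived from the reported HandScan–DAS28 correlation of 0.42.* That correlation is with DAS28, whereas the trial applies a Boolean rule to 44 joints. Remission prevalence and dependence between visits would also have to be assumed, and the result would count discordant remission status, not differing medication steps.
- *Later allocations become predictable.* With blocks of 4 per center, one third of positions (8 of 24 over the six possible blocks) are fixed by the preceding ones. Using this would require correct inference of every earlier arm in the block before the next patient enters, which the documents do not show.

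**Conclusion.** The point holds in limited form. The allocation list is concealed. The guiding method is not reliably concealed from site staff who see the clinical findings and the open-label advice, at visits before a switch where the two rules would give different steps. The unqualified blinding statements in the Abstract, Methods/design, Randomization and Discussion therefore go further than the remission definitions, the treatment steps and the software description allow.

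The logical conclusion rests only on text in the article. Its frequency cannot be established from the article: the range of 26.5% to 88.2% over six visits depends entirely on an assumed 5% to 30% per visit and on independence. That discordance is foreseen is clear from the switch rule itself. No bias in the HAQ comparison is demonstrated.

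**What to change.** 1. Have joint counts and PGA entered and locked before the HandScan result is available, and the HAQ completed before the medication advice is shown. This protects the data of the same visit, even though knowledge carried over from earlier visits remains.
2. State who operates the scan, who counts joints, who enters data and who receives the advice. Where feasible, keep the HandScan score from the joint assessor and the prescriber. This is a partial remedy, because the clinical findings and the advice alone can be enough.
3. Replace the unqualified term double-blind with a statement that the allocation list is concealed but that the guiding method can be inferred at decision-discordant visits. Qualify the Discussion's sentence on switches in the same way.

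The third change is the essential one and needs only rewording. The first costs a site instruction and a change in entry order. The application was developed under medical-software standards and the trial was already recruiting, so a built-in lock may need retesting; an instruction can set the same order meanwhile. Hiding the score screen is less certain, because it is the HandScan's own interface. The remaining cost is a less favourable blinding claim in the report. No treatment rule changes.

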### Assessments

Patients will visit the outpatient clinics monthly (Fig. 1). At each visit, disease activity will be measured, to ensure blinding both with HandScan and DAS44, consisting of serum CRP, a 44 joints assessment for swelling and tenderness, and a PGA (VAS 0–10 cm, 10 = worst). At baseline and 3, 6, 12, and 18 months patients will fill out the HAQ (first outcome), the Short Form Health Survey (SF36), EuroQol (EQ5D), and the questionnaire on direct and indirect costs (second outcome). Direct costs (health care) and indirect costs (loss of paid and household productivity) will be calculated from questionnaires, including the Health and Labour questionnaire [13]. Radiographs in the antero-posterior direction of hands, wrists, and feet will be obtained at baseline and 18 months (second outcome). The current gold standard for scoring these radiographs is the Sharp/van der Heijde scoring method [11]. This method scores erosions (score 0–5 per region) and joint space narrowing (score 0–4 per region) of these joints and sums the scores to the SHS score, ranging from 0 to 448. A newly developed fully automated radiographic scoring system of hand and wrist joints is also applied to quantify changes in the joint space width over time.

**Fig. 1 Fig1:**
[figure not shown]
SPIRIT figure, trial visits, and assessments

At each visit, patients’ blood will be sampled (10 cc) for CRP evaluation and to monitor for adverse-effects of medication. Data from all centers are collected digitally in one eCRF, through the online data-gathering tool *Research Online* (developed by UMC Utrecht Julius Center).

### Definitions of remission

Aimed at predefined remission criteria, treatment is intensified in a similar fashion for both arms, according to a predefined schedule. In the DAS arm, remission is defined based on the ACR/EULAR 2011 Boolean remission criteria, all of which must be met [14]:TJC ≤ 1 of 44 joints: sternoclavicular, acromioclavicular, shoulder, elbow, wrist, metacarpophalangeal (MCP), proximal interphalangeal (PIP), metatarsophalangeal (MTP), knee, and ankle jointsSJC of 30 small joints (MCP, PIP, and MTP joints) ≤ 1 AND SJC of 14 large and other joints (sternoclavicular, acromioclavicular, shoulder, elbow, wrist, knee, and ankle joints) = 0CRP ≤ 1 mg/dlPGA ≤ 1 (on VAS 0–10 cm, 10 = worst)

In the HandScan arm, remission is defined based on the following HandScan criteria, all of which must be met:Total optical joint score per patient ≤ 11(based on ROC curves in a comparative study with DAS28 and ultrasonography) [6, 7]≤ 1 joint per patient with an optical score of > 1

The optical joint scores are shown by the HandScan shortly after assessment (see screen shot of the HandScan in Fig. 2).

**Fig. 2 Fig2:**
[figure not shown]
The HandScan user interface; total and individual optical joint scores. The total optical joint score of 9.43 (*blue arrow*) meets the HandScan remission criterion for total score. Individual optical joint criteria are shown below the picture. Three joints (*green arrows*) exceed the individual optical joint score criterion (> 1). Considering the HandScan remission criteria (total optical spectral transmission (OST) score ≤ 11 AND a maximum of one joint with OST > 1), this (test) patient is not in remission

### Treatment strategy

After randomization, in both arms all patients will initiate a methotrexate (MTX)-based tight-control strategy, with 10 mg per week MTX orally as starting dose and with prednisolone (PRED) fixed dose of 10 mg/day orally [15]. Patients are evaluated monthly and at each visit a dosage decision is made based on efficacy and adverse events. In case remission is not achieved, MTX dose will be increased at each monthly visit until either remission or the maximum tolerable dose (MTD) is reached (Table 2). Escalation steps are 15, 20, 25, 30 mg MTX/week orally, followed by 30 mg MTX/wk (or MTD) subcutaneously. At a dose of MTX of 25 mg/week (or MTD of MTX), hydroxychloroquine (HCQ) 400 mg/day for patients ≥ 60 kg (or 200 mg/day for patients ≤ 60 kg) will be added. After the final escalation step of MTX, in case of no remission, tumor necrosis factor inhibitor (anti-TNF), e.g., adalimumab 40 mg s.c. every 2 weeks, will be added to the MTX therapy, while HCQ will be stopped.

**Table 2 Tab2:** Intensifying treatment strategy in case remission is not achieved

Week	MTX*	PRED	HCQ	Anti-TNF
	mg/week	10 mg/day	400 mg/day	
0 = start of study	10	+	–	–
+ 4	15	+	–	–
+ 4	20	+	–	–
+ 4	25	+	+	–
+ 4	30	+	+	–
+ 4	Same dose s.c.	+	+	–
+ 4	Same dose s.c.	+	–	+
+ 4	Same dose s.c.	+	–	+
+ 4	Same dose s.c.	+	–	+

If remission is not achieved after each period of 4 weeks, treatment is intensified stepwise. *MTX* methotrexate, *PRED* prednisolone, *HCQ* hydroxychloroquine, *anti-TNF* anti-tumor necrosis factor, *s.c.* subcutaneously

*Same dose s.c.: the dose at the previous step, given s.c. at a dose of 30 mg, or earlier. In case of dose-dependent adverse reactions to MTX (> 10 mg/week), previously tolerated dose will be administered s.c., and this will then be the maximum tolerable dose (MTD) for that patient. Further intensifying treatment would be adding or continuing HCQ. HCQ is given for three consecutive months in every scenario

If remission is achieved, treatment will be continued unchanged. If remission persists over three consecutive months (sustained remission (SR)), treatment intensity will be de-escalated by one step; following de-escalation steps will be taken every time remission persists for another 3 months (Table 3). De-escalation steps will vary with the dosages at remission (Fig. 3 and Table 3), but the first de-escalation step will always be tapering PRED to 7.5 mg/day. If disease activity flares (i.e., loss of remission according to the remission criteria), patients will return to the previous dosages at which they achieved remission and medication will be escalated until remission is achieved again. If disease activity flares during medication-free remission, patients will return to MTX 10 mg/week and PRED 10 mg/day (medication at start of the study) and medication will be escalated until remission is achieved again. The treatment protocol is derived from the second Computer Assisted Management in Early Rheumatoid Arthritis trial (CAMERA-II) [15]. Co-medications are calcium and vitamin D supplementation and a bisphosphonate during PRED treatment, and folic acid to prevent MTX toxicity; dosages of co-medication are according to guidelines. Each center will provide their own preferred anti-TNF.

**Table 3 Tab3:** Tapering and stopping treatment in case remission is maintained after 12 weeks of unchanged treatment*

	Weeks of remission	MTX	PRED	HCQ	Anti-TNF
		(mg/week)	(mg/day)	(mg/day)	
MTX + PRED	< 12	Same dose	10	–	–
	12	Same dose	7.5	–	–
	> 12, every 12 weeks	Decrease with 5 mg/week until 10 mg/week	7.5	–	–
	+ 12	10	5	–	–
	+ 12	5	5	–	–
	+ 12	5	2.5	–	–
	+ 12	5	Stop	–	–
	+ 12	2.5	–	–	–
	+ 12	Stop	–	–	–
MTX + PRED + HCQ	< 12	Same dose	10	400	–
	12	Same dose	7.5	400	–
	> 12, every 12 weeks	Decrease with 5 mg/week until 10 mg/week	7.5	stop	–
	+ 12	10	5	–	–
	+ 12	5	5	–	–
	+ 12	5	2.5	–	–
	+ 12	5	Stop	–	–
	+ 12	2.5	–	–	–
	+ 12	Stop	–	–	–
MTX + PRED + aTNF	< 12	Same dose	10	–	Same dose
	12	Same dose	7.5	–	Same dose
	> 12,	Same dose	7.5	–	½ frequency^#^
	every 12 weeks	One step back until 10 mg/week	7.5	–	Stop
	+ 12	10	5	–	–
	+ 12	5	5	–	–
	+ 12	5	2.5	–	–
	+ 12	5	Stop	–	–
	+ 12	2.5	–	–	–
	+ 12	Stop	–	–	–

* Tapering treatment depends on the combination of medication at the moment of sustained remission. ^#^ In this multi-center study, centers prescribe their preferential anti-TNF; therefore, a more global approach to decreasing aTNF dose is applied—reduction of frequency of administration, i.e., extension of dosing interval

*MTX* methotrexate, *PRED* prednisone, *HCQ* hydroxychloroquine, *anti/a-TNF* anti-tumor necrosis factor

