### Adverse reactions to DMARDs

In case of adverse reactions to initial dose of MTX (10 mg/week), MTX will be substituted with leflunomide (LEF) 20 mg/day. If LEF is well tolerated and remission is not achieved, HCQ will be added; next escalation steps are as described above (Table 2). Patients that switch to LEF and are consequently unable to achieve remission will reach anti-TNF treatment faster than patients on MTX (with the exception of an MTD). In case of adverse reactions to MTX at dosages ≥ 10 mg/week, the last well-tolerated dose will be administered subcutaneously and considered to be the MTD. If remission is not achieved, treatment will be intensified according to Table 2, e.g., at a MTD of MTX 15 mg/week subcutaneously, HCQ will be added.

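### The hydroxychloroquine weight bands overlap at exactly 60 kg, and Tables 2 and 3 print 400 mg/day without the weight condition that the text gives

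*Protocol article*

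**What the plan says.** All places are in the Protocol article.

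- **Treatment strategy, text.** When methotrexate (MTX) reaches 25 mg/week or the maximum tolerable dose without remission, HCQ is introduced: "400 mg/day for patients ≥ 60 kg (or 200 mg/day for patients ≤ 60 kg) will be added".
- **Table 2 (intensifying treatment).** The sub-header over the prednisolone and HCQ columns reads "10 mg/day 400 mg/day". The rows beneath carry only plus and minus signs. The footnote on HCQ concerns duration: "HCQ is given for three consecutive months in every scenario".
- **Table 3 (tapering), block for MTX, prednisolone and HCQ.** The row for under 12 weeks of remission reads "Same dose 10 400" and the row for 12 weeks reads "Same dose 7.5 400", the last figure being HCQ in mg/day. HCQ is then stopped. The footnote says "Tapering treatment depends on the combination of medication at the moment of sustained remission" and does not mention weight.
- **Adverse reactions to DMARDs.** After a switch to leflunomide, HCQ is added with no dose given: "If LEF is well tolerated and remission is not achieved, HCQ will be added; next escalation steps are as described above (Table 2").
- **Software application section.** At each visit "the patient identification number, year of birth, and parameters for both clinically and HandScan-assessed disease activity will be entered into the application". Body weight is not named in that list.

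**The concern.** HCQ is a scheduled step for every patient who is still not in remission at MTX 25 mg/week or at the maximum tolerable dose, so its dose rule is an operative instruction. As printed, the rule has two defects. At one weight it returns two answers. Below that weight, the text and the tables show different figures, and no footnote says that the table entry stands for the weight-based rule.

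What is at stake is consistent dosing of individual patients. A site or programmer working from the tables could arrive at a different dose from one working from the text. The leflunomide route adds to this, because it gives no HCQ dose of its own and points to Table 2 for the steps that follow.

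**Working it through.** There is no sample-size or power figure to reproduce. The check is a comparison of the passages, band by band.

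**Step 1. Overlap.** The two conditions are weight ≥ 60 kg and weight ≤ 60 kg. They share exactly one value, 60 kg, where the rule returns both 400 and 200 mg/day.

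**Step 2. Text against tables.**

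| Body weight | Text | Table 2 header | Table 3, rows < 12 and 12 weeks | Table / text |
|---|---|---|---|---|
| below 60 kg | 200 mg/day | 400 mg/day | 400 mg/day | 400/200 = 2.0 |
| exactly 60 kg | 400 and 200 mg/day | 400 mg/day | 400 mg/day | 1.0 or 2.0 |
| above 60 kg | 400 mg/day | 400 mg/day | 400 mg/day | 1.0 |

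The mismatch is therefore confined to patients at or below 60 kg.

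**Step 3. Is the table figure only shorthand?** In Table 2 this is plausible: 400 mg/day is a column label, the cells show only when HCQ is given, and the weight rule stands in the paragraph just above. Table 3 is harder to read that way. Where a dose differs between patients at the moment of remission (MTX, anti-TNF), its first rows say that the dose stays the same. Where a dose is fixed for all (prednisolone 10, then 7.5 mg/day), they print a number. HCQ gets a number, so by the table's own convention 400 looks like a fixed dose.

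**Step 4. Table 3 against the remission rule.** The text introducing Table 3 says that treatment is left unchanged once remission is reached. For a patient who remitted on 200 mg/day, unchanged means 200, while the first row of the block prints 400. The two statements do not match for that patient.

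**Step 5. How many patients?** The number is the product of the patients randomised, the share at or below 60 kg, and the share of those who reach an HCQ step. The documents give neither share, so no count can be derived.

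**The case against.** The strongest reply is that this is a boundary slip plus two tables that omit a qualifier, and that a careful reader would never be misled. Much of that stands.

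- **A reader might infer that the tables prescribe 400 mg/day for everyone.** They do not say so. They omit the weight condition, and a specific rule printed directly above Table 2 would normally be taken to qualify its header.
- **A reader might infer that a light patient in remission would have the dose doubled.** The documents argue against it. Treatment is to continue unchanged, Table 3's title speaks of unchanged treatment, the de-escalation steps are said to depend on the dosages at remission, and the first step is always a reduction of prednisolone. What remains is a printed figure that does not match those rules.
- **A reader might infer that the software applies the flat 400 mg/day because weight is not a listed input.** The list covers what is entered at each visit. The Randomization section separately refers to baseline clinical data being entered, and these could include weight. The coded dose is not shown, and the article condenses a fuller protocol that is not at hand.
- **A reader might infer that adherence can no longer be judged.** The text gives a single dose at every weight except exactly 60 kg, so this goes too far.

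What the reply does not remove is the overlap itself, the lack of any note linking the tables to the weight rule, and Table 3's use of a number where it describes other patient-specific doses as kept the same.

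**Conclusion.** The HCQ dosing passages are inconsistent and wrong as written, at a minor level. The text assigns two doses at exactly 60 kg. Read literally, both tables show twice the text's dose for patients below 60 kg. In Table 3 the figure also conflicts on its face with the rule of unchanged treatment in remission, although an actual increase is unlikely.

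The twofold figure rests on a literal reading of the tables; if they are shorthand for the text, only the overlap at 60 kg remains. The number of patients concerned is unknown. The Objectives section makes treatment and treatment steps identical in the two arms, so the inconsistency is not in itself a source of bias between them. It does not enter the sample-size calculation or the primary analysis of HAQ at 18 months. It matters as a question of dosing consistency and patient safety. Nothing here implies a view on which dose or weight limit is right.

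**What to change.** The sponsor should reconcile the Treatment strategy text with Tables 2 and 3:

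1. State the weight bands so that they do not overlap. Which dose applies at 60 kg is for the investigators to decide.
2. Make the HCQ entries in both tables agree with the rule so settled. If the weight-based rule is the intended one, a footnote in Table 2 could refer to it, and the two Table 3 rows could use the same-dose wording already used there for MTX and anti-TNF.
3. Confirm that the decision software applies the reconciled rule and, if that rule depends on weight, that it receives body weight.

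The cost is a few words in the text and tables and one software check. Sample size, data collection for the outcomes and the planned analyses do not change. The article describes the trial as recruiting, so the check is best made promptly.
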